#### 5.3.3 Systemic inflammation

It was reported that in some COVID-19 patients, the immune response elicited against SARS-CoV 2 results in an increase in systemic inflammatory cytokines, which may eventually progress to a “cytokine storm,” followed by multi-organ system dysfunction (45). In fact, some of the severe manifestations of COVID-19 are linked to the excess of circulating pro-inflammatory cytokines: acute respiratory distress syndrome, thromboembolic diseases such as acute ischemic strokes caused by

[figure not shown]

large vessel occlusion and myocardial infarction, encephalitis, acute kidney injury, and vasculitis (46). The chronic activation of pro-inflammatory pathways documented in the elderly, especially men, and named “inflamm-aging”, represents a risk factor *per se* for the development of COVID-19 complications (47).

We believe the restoration of a functional IFN-I response, through the administration of IFN- $\beta$ 1a during the early phase of SARS-CoV 2 infection, may affect systemic hyper inflammation both directly, by means of the immunomodulatory properties of the cytokines, and indirectly as an effect of reduced SARS-CoV 2 replication.

The level of inflammatory markers known to have a prognostic role in COVID-19 progression, such as IL-6, CRP, TNF- $\alpha$  (48) together with some endothelial cell adhesion molecules whose expression levels correlate with COVID-19 severity (FKN, VCAM-1, ICAM-1, VAP-1 (49)), will be analysed in the blood collected from IFN and control arm before and 10 days after enrolment. Data will be integrated with the results of routine lab analysis on coagulations factors (Fibrinogen, D-dimers) also involved in COVID-19 pathogenesis. The comparative analysis between groups will address treatment-induced modulations and possible correlation with clinical outcome.

#### 5.4 Statistical hypothesis

The trial power has been calculated by the ISS group. The study was powered to independently assess a potential benefit of IFN- $\beta$ 1a compared with control arm (no specific antiviral treatment besides standard of care) on rate of progression of NEWS2 score lasting more than 5 days.

Sample size was calculated according to the primary endpoint of the study. In particular, the sample size calculation is based on the assumptions of an at least 35% difference in the percentage of patients undergoing disease progression between IFN- $\beta$ 1a and control arm. A sample size of 60 patients total (40 in the IFN- $\beta$ 1a-treated arm and 20 in the control arm, according to a 2:1 randomization ratio) will be needed to provide 80% power at significance level of 5% to detect the difference of patients undergoing disease progression between a group 1 proportion of 0.15 (IFN- $\beta$ 1a + standard of care) and a group 2 proportion of 0.50 (standard of care).

[figure not shown]

**Sample Size: ANTIICIPATE trial**

|                                             |     |
|---------------------------------------------|-----|
| Two-sided significance level ( $1-\alpha$ ) | 95  |
| Power ( $1-\beta$ , % chance of detecting)  | 80  |
| Ratio of sample size, Unexposed/Exposed     | 0.5 |
| Percent of Unexposed with Outcome           | 50  |
| Percent of Exposed with Outcome             | 15  |
| Risk Ratio                                  | 0.3 |
| Risk difference                             | -35 |

**Kelsey Fleiss Fleiss (CC)**

|                       |    |           |    |
|-----------------------|----|-----------|----|
| Sample Size - Exposed | 39 | 40        | 48 |
| Sample Size-Unexposed | 20 | 20        | 24 |
| Total sample size     | 59 | 60 | 72 |

## 6. Study design

Randomized, Open-Label, Controlled, Phase II Study. Patients, who satisfy all inclusion criteria and no exclusion criteria, will be randomly assigned to one of the two treatment groups in a ratio 2:1. Randomization will be stratified by gender. Stratified randomization will balance the presence of male and female in both study arms. The planned study duration is 12 months including study set up, enrollment, follow up and data analysis as indicated in Appendix 3.

## 7. Study Population

Male and female adults aged 65 years or older with newly diagnosed mild COVID-19 are eligible for the study.

[figure not shown]

## 7.1 Case definition

For the purpose of the study, the following definition is applied: a case of COVID-19 is a person with detectable SARS-CoV 2 genes, as determined by PCR on an adequate sampling of upper respiratory tract.

## 7.2. Criteria for eligibility

### 7.2.1 Inclusion criteria

- $\geq 65$  years of age at time of enrolment;
- Laboratory-confirmed SARS-CoV 2 infection as determined by PCR, in any specimen  $< 72$  hours prior to randomization;
- Subject (or legally authorized representative) provides written informed consent prior to initiation of any study procedures;
- Understands and agrees to comply with planned study procedures;
- Agrees to the collection of nasopharyngeal swabs and venous blood samples per protocol;
- Being symptomatic for less than 7 days before starting therapy;
- NEWS2 score  $\leq 2$

### 7.2.2 Exclusion criteria

- Hospitalized patients with illness of any duration, and at least one of the following:
  - Clinical assessment (evidence of rales/crackles on exam) AND SpO2  $\leq 94\%$  on room air at rest or after walking test,OR
  - Acute respiratory failure requiring mechanical ventilation and/or supplemental oxygen;
- Patients currently using IFN-beta (e.g., multiple sclerosis patients);
- Patients undergoing chemotherapy or other immunosuppressive treatments
- Patients with chronic kidney diseases;
- Known allergy or hypersensitivity to IFN (including asthma);
- Any autoimmune disease (resulting from patient anamnesis);
- Patients with signs of dementia or neurocognitive disorders;

[figure not shown]

- Patients with current severe depression and/or suicidal ideations;
- Being concurrently involved in another clinical trial;
- HIV infection (based on the anamnesis);
- Use of any antiretroviral medication;
- Impaired renal function (eGFR calculated by CKD-EPI Creatinine equation  $< 30$  ml/min);
- Presence of other severe diseases impairing life expectancy (e.g. patients are not expected to survive 28 days given their pre-existing medical condition);
- Any physical or psychological impediment in a patient that could let the investigator to suspect his/her poor compliance;
- Lack or withdrawal of informed consent

### 7.3 Recruitment strategy

The management of elderly patients with COVID-19 needs to take into consideration the presence of comorbidities that increases their fatality risk, but it is also affected by the epidemiological situation of SARS-CoV 2 infection (see Feasibility section). Our study plans to enroll either hospitalized and non-hospitalized newly diagnosed COVID-19 patients, as well as patients hosted in long-stay residential care homes.

The Special Unit for regional continued care (USCAR), having the role of early detecting clusters of infection within Regione Lazio, will be responsible for screening and enrolling eligible patients that after SARS-CoV 2 positivity notification are not hospitalized, but remain in isolation at home or in a long-stay residential care homes. When dealing with patients older than 65, USCAR will be responsible of informing the patient of the current study, of having the Informed Consent signed and of collecting the blood sample to assess eligibility criteria. After the enrolment, the patient will be followed by a dedicated USCAR team that will: i) give to the patient/family-caregiver the kit of devices for home monitoring (i.e., 1 pulse oxymeter, 1 digital sphygmomanometer, 1 thermometer), ii) perform training for the use of devices, iii) perform treatments and collect samples for monitoring patients according to the timeline described in Appendix 2. The USCAR team will receive daily updates from non-hospitalized patients to determine their NEWS2 score values.

[figure not shown]

Patients that, at discretion of the general practitioner, are directed to Spallanzani Hospital for hospitalization, will be there assessed for inclusion/exclusion criteria and, in case of eligibility, enrolled in the study. Patients will be monitored according to standard hospital protocol in addition to the timeline described in Appendix 2.

## 8. Intervention

### 8.1 Experimental Drug and justification for dose

Rebif® (interferon beta-1a) is a disease-modifying drug used to treat relapsing forms of multiple sclerosis (MS) and is similar to the IFN-beta protein produced by the human body. It was approved in Europe in 1998 and it is used in more than 90 countries worldwide. While current posology of Rebif in MS (12 MIU 3 times/week) is capable of balancing the neural inflammation typical of MS, the dosing and schedule of Rebif® administration in this study were selected by taking into consideration some features of IFN-I, emerged from many years of clinical use of these cytokines. In fact, several clinical studies reported that an Interferon-induced immune adjuvant activity could be observed already after the administration of intermittent low doses of the cytokine in both cancer and antiviral settings (15,50–52). Instead, the continuous stimulation of IFN-I signaling, exerted by high serum levels of the cytokine, can result in diminished treatment efficacy due to the emergence of refractoriness phenomena caused by receptor internalization/degradation as well as the rapid induction of UBP43 and SOCS negative regulators (4), immunosuppression and can also result in relevant side effects.

With the aim to tailor the treatment schedule to the early phase of SARS-CoV 2 infection in elderly patients, we selected 3 MIU of IFN-β1a as a dose expected to exploit IFN-mediated antiviral and immunomodulatory properties of the cytokine without causing relevant toxicity or inducing refractoriness phenomena (53).

### 8.2 Treatment arms

**Control arm.** No specific antiviral treatment besides standard of care.

[figure not shown]

**Treatment arm.** 11ug (3MIU) of IFN- $\beta$ 1a will be injected subcutaneously at day 1, 3, 7, and 10 in addition to standard of care. The drug solution, contained in a pre-filled cartridge, will be injected by means of the RebiSmart electronic injection device, as described in Appendix 6.

### 8.3 Standard patients monitoring

Patients will be daily evaluated for body temperature, respiratory rate, oxygen saturation, blood pressure, pulse/heart rate and AVPU response. The NEWS2 score will be then calculated following the table 2. Additional measurements are allowed whenever any sign of disease progression appears. In case of multiple measurements within a day, the highest score will be considered for patient assessment.

Table 2. NEWS2 Score

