### 5.1.1 Primary endpoint and outcome

Primary endpoint of the study is the proportion of patients experiencing a disease progression, during at least 5 days, according to the National Early Warning Score (**NEWS2**). The **NEWS2** score is a standardized approach aimed at promptly detecting signs of clinical deterioration in acutely ill patients and establishing the potential need for higher level of care. It is based on the evaluation of vital signs including respiratory rate, oxygen saturation, temperature, blood pressure, pulse/heart rate, AVPU response. The resulting observations, compared to a normal range, are combined in a single composite “alarm” score. Any other clinical sign clearly indicating a disease worsening will be considered as disease progression.

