### 9.2 Blinding

This is an open-label study. After the randomization, patient will be notified whether will receive or not the experimental drug.

[figure not shown]

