## 10. Statistical Plan

The primary analysis will be carried out on the primary endpoint on the intention-to-treat (ITT) population defined as all patients randomized receiving at least one dose of treatment.

The percentage of patients undergoing disease progression defined on rate of progression of NEWS2 score lasting more than 5 days will be calculated in two arms (IFN- $\beta$ 1a + standard of care vs standard of care) of the trial. For persons who died, a conservative approach will be adopted and death will be considered an event. The effect of treatment will be estimated through a logistic regression model including a dummy variable for treatment. The effect of treatment will be estimated through multivariable logistic regression model by accounting for the following

[figure not shown]

covariates: age, gender, co-morbidities. Moreover, NEWS2 score at baseline and setting of recruitment will be also considered.

All primary and secondary analyses will be carried out both on ITT population and on per-protocol population. Per-protocol population includes all subjects who were included in the ITT population that received the treatment as defined in the protocol and who completed the study with no major protocol violations.

Kaplan-Meier survival analysis and Cox proportional hazards model will be used for time-to-event data. The following covariates will be included in the Cox model: age, gender, co-morbidities. Moreover, NEWS2 score at baseline and setting of recruitment will be also considered. For the secondary endpoint ICU-free days, a competing risk model will be adopted considering death a competing event, following the method proposed by Fine and Gray (57). Moreover, the median difference will be reported.

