| TABLE 4 - REBIF common AE                                                                                                                                                                              |                                                                                                                                                                                                                                         |
|--------------------------------------------------------------------------------------------------------------------------------------------------------------------------------------------------------|-----------------------------------------------------------------------------------------------------------------------------------------------------------------------------------------------------------------------------------------|
| Very common ( $\geq 1/10$ )                                                                                                                                                                            | Common ( $\geq 1/100$ to $< 1/10$ )                                                                                                                                                                                                     |
| Neutropenia, lymphopenia, leukopenia, thrombocytopenia, anaemia
Asymptomatic transaminase increase

Headache
Injection site inflammation, injection site reaction, influenza-like symptoms | Diarrhoea, vomiting, nausea
Severe elevations in transaminases
Pruritus, rash, erythematous rash, maculo-papular rash, alopecia

Myalgia, arthralgia
Depression, insomnia
Injection site pain, fatigue, rigors, fever |

| TABLE 5 - Routine laboratory test parameters |                 |
|----------------------------------------------|-----------------|
| Haemoglobin                                  | ALT/SGPT        |
| Haematocrit                                  |                 |
| Full Blood count                             |                 |
| Creatinine                                   |                 |
| Sodium                                       | AST/SGOT        |
| Potassium                                    | ESR             |
| Procalcitonin                                | Total bilirubin |
|                                              | Urea (BUN)      |
| Glucose                                      | Albumin         |

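### Scoring each day by the highest NEWS2, with uncapped symptom-triggered readings in an open-label trial, makes the primary endpoint depend on how often a patient is measured

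*Protocol*

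**What the plan says.** - **Daily value (protocol 8.3).** NEWS2 is assessed daily. "Additional measurements are allowed whenever any sign of disease progression appears", and "In case of multiple measurements within a day, the highest score will be considered for patient assessment". The section sets no clock time, no maximum number of readings, and no timing relative to the injection or to the paracetamol that 8.4 allows.
- **Endpoint (5.1.1, 5.4, 10).** Section 5.1.1 defines "the proportion of patients experiencing a disease progression, during at least 5 days". Section 10 has it "defined on rate of progression of NEWS2 score lasting more than 5 days", as does 5.4 in substance. No size of NEWS2 increase is given, and consecutive days are not stated. A second route has no duration: "Any other clinical sign clearly indicating a disease worsening will be considered as disease progression".
- **Who measures.** At home, the patient, a caregiver or a family member takes the readings (8.3). For patients in hospital, "Patients will be monitored according to standard hospital protocol in addition to the timeline described in Appendix 2" (7.3). Hospital patients may go home during follow-up (8.3).
- **Blinding and allocation.** "After the randomization, patient will be notified whether will receive or not the experimental drug" (9.2). Randomisation is stratified by sex only (9.1). Section 10 says that setting of recruitment will be considered in the model.
- **Drug reactions.** Doses fall on days 1, 3, 7 and 10 (8.2). Section 9.4.1 lists influenza-like symptoms as very common (at least 1/10). The common group (1/100 to below 1/10) includes "Injection site pain, fatigue, rigors, fever". NEWS2 gives 1 point for 38.1–39.0 °C, 2 points from 39.1 °C, and 1 point for a pulse of 91–110.

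**The concern.** The maximum of several readings can only stay level or rise as readings are added. When the number of readings is uncapped and prompted by suspected worsening, the daily score reflects both the illness and how closely someone is watching.

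The protocol leaves room for watching to differ:

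- **By arm.** Everyone knows the allocation. At home the same trial team gives the injections, and on day 7 Appendix 2 lists an injection for the interferon arm but no sampling in either arm. Treated patients may therefore have one more staff contact.
- **By setting.** Hospital routine comes on top of the study schedule.
- **By drug reaction.** Fever and a raised pulse can add NEWS2 points in one arm only.

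The design expects 0.15 × 40 + 0.50 × 20 = 16 primary events, so a few reclassified patients would matter.

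**Working it through.** **1. The plan's own figure.** Inputs from 5.4: 0.50 against 0.15, 2:1 allocation, two-sided 5%, 80% power. Fleiss formula with k = 2 and pooled rate (0.50 + 2 × 0.15)/3 = 0.267:

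n(control) = [1.96 × √(1.5 × 0.267 × 0.733) + 0.842 × √(0.25 + 0.1275/2)]² / 0.35² = 19.2, rounded up to 20.

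This gives 20 + 40 = 60, as stated. Power at 20:40 is 81.6%. The sample size is not at fault.

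**2. Effect of the number of readings.** Assumptions, since the protocol sets no NEWS2 increase: one reading is raised with probability q, readings and days are independent, and the qualifying days are consecutive. With k readings a day, the day is flagged with probability Q = 1 − (1 − q)^k. The chance of at least one run of 5 or 6 flagged days in 28 is then computed exactly, tracking the current run length day by day. The two run lengths match the wordings in 5.1.1 and 10.

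| q | k | Q | run ≥ 5 days | run ≥ 6 days |
|---|---|---|---|---|
| 0.2 | 1 | 0.200 | 0.6% | 0.1% |
| 0.2 | 2 | 0.360 | 9.2% | 3.3% |
| 0.2 | 3 | 0.488 | 31.7% | 15.8% |
| 0.3 | 1 | 0.300 | 4.1% | 1.2% |
| 0.3 | 2 | 0.510 | 37.1% | 19.6% |
| 0.3 | 3 | 0.657 | 76.3% | 56.6% |

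**3. Correlated readings.** Simulated on a latent normal scale, run ≥ 6 days:

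- Patient variance 0.3 and day variance 0.2 (assumed): about 4%, 13% and 21% for k = 1, 2, 3 at q = 0.2; about 10%, 27% and 39% at q = 0.3.
- Within-day correlation 0.8 with independent days (assumed): k = 3 gives about 1.5% at q = 0.2 and 9% at q = 0.3, against 0.1% and 1.2% for k = 1.

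The gradient survives, but its size depends heavily on the correlation.

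**4. The fever route.** Doses on days 1, 3, 7 and 10; the reaction length is assumed because the protocol gives none.

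| Reaction length | Days touched | Longest run |
|---|---|---|
| 1 day | 4 | 1 |
| 2 days | 8 (1–4, 7–8, 10–11) | 4 |
| 3 days | 11 (1–5, 7–12) | 6 |

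If days must be consecutive, fever alone reaches the rule only with reactions of about 3 days. If days may be summed, 2-day reactions already pass it.

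Fever can also join up with background readings. Take k = 1, run ≥ 6 days, and a reaction probability r on each of the eight days touched by 2-day reactions, so that a day is flagged with probability 1 − (1 − q)(1 − r). At r = 0.6, false events are about 3% (q = 0.2) or 9% (q = 0.3). At r = 0.1 they move only from 0.12% to 0.22% (q = 0.2) or from 1.2% to 1.7% (q = 0.3).

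**5. What a difference between arms would cost, if one arose.**

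- False progression in 5% of interferon non-progressors makes that rate 0.15 + 0.05 × 0.85 = 0.1925, and power falls from 81.6% to 68.8%. At 10% the rate is 0.235 and power is 54.3%.
- With no true effect and a rate of 0.30 in both arms, extra detection in 5% of control non-progressors makes the control rate 0.30 + 0.05 × 0.70 = 0.335. The chance of a significant result favouring interferon is then 4.8%, against a nominal 2.5%.

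**The case against.** The strongest reply is that the worst value of the day is a pre-specified, conservative convention applied identically in both arms, and that several days of persistence filter out isolated peaks. Setting differences are balanced in expectation by randomisation and may be adjusted for. Most of this stands, but it does not close the point. The same maximum taken over different numbers of readings is not the same measurement. Recruitment setting does not follow a patient who is discharged mid-study, and no planned covariate captures re-measurement related to arm. The persistence rule is also loosely fixed: two durations, no stated increase, and no statement on consecutive days.

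A reader might infer more than the documents support:

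- **That the result is biased in a known direction.** Nothing shows unequal reading between arms. Drug fever would count against interferon, and closer watching of untreated controls would count in its favour.
- **That interferon fever will by itself produce many events.** This needs long reactions or summed days. A reaction probability of 0.6 has no source in the protocol: 9.4.1 puts fever and rigors below 1/10, and it does not say how often influenza-like symptoms bring a scoring temperature. Those are product-label rates, and 8.1 contrasts the usual multiple sclerosis posology with the lower dose used here.
- **That the rule can hide progression.** A maximum never lowers a score. Masking could arise only indirectly, for example if false interferon events diluted a real benefit or if some patients were measured less.
- **That nothing could be done later.** Appendix 4 records the NEWS2 components by date, so an analysis without temperature is possible.

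The diary template cannot be read in the copy available and may specify reading times.

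**Conclusion.** The point holds as a weakness in how the primary endpoint is measured, and correcting it is a cheap improvement. Under 8.3, the probability of being classified as progressing rises with the number of readings, and that number is uncapped, prompted by suspected outcome and open to influence by known allocation and by care setting. Persistence of about 5 days limits the effect but does not remove it.

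The size cannot be fixed from the documents. Across the assumptions tried at q = 0.2, going from one to three readings a day raises the chance of a run of at least 6 days from 0.1% to between 1.5% and 15.8%, or from about 4% to 21% with patient-level correlation. These figures rest on assumed reading probabilities, assumed correlation and several readings on every day, whereas 8.3 foresees extra readings only on suspicion. They show the mechanism and are not a forecast for this trial.

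**What to change.** In 8.3, state that the primary endpoint is classified from one scheduled daily NEWS2 at a fixed time, taken before the injection on dosing days, with the same timing in both arms and in all settings. Flag scheduled and unscheduled readings separately in the diary and the eCRF. Keep extra readings for care and safety, and report the highest-of-day score as a sensitivity analysis.

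The cost is wording in 8.3, the diary and the eCRF. Appendix 2 already requires a daily NEWS2, so no measurements are added, and the sample size is unchanged. The downside is that peaks between scheduled readings no longer count towards the primary endpoint, which matters little when progression must persist for about 5 days. The change does not stop a reaction that lasts into the next scheduled reading. It also leaves the separate route through other clinical signs in 5.1.1 as it is.
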